#### 8.8.6.5 Atrial Fibrillation Ablation Intraoperative Data Retention

During the radiofrequency ablation of atrial fibrillation, the three-dimensional ablation focus distribution map when the bilateral pulmonary veins reach electrical isolation, the intracardiac electrogram record of the multipolar catheter in the pulmonary vein, the non-pulmonary vein trigger focus outside the PVI and the matrix modified ablation focus distribution map should be saved respectively. Save pictures (in the recommended .jpeg format) or videos (in the recommended .avi or .mp4 format).

#### 8.8.6.6 LAAO after ablation

Withdraw the cold saline ablation catheter, send the 5Fr pigtail catheter through the sheath to LAA, perform LAA angiography, measure the size of auricle, and perform LAAO (see 8.8.7.1~8.8.7.5 for details). The operation was ended when the occlusion effect was satisfactory.

### 8.8.7 Surgical protocols for the occlusion-first group

#### 8.8.7.1 LAA angiography

LAA angiography was performed at least 2 orthogonal projection angles (30 °+20 ° in the right anterior oblique position, 30 °+20 ° in the right anterior oblique position, 20 ° in the right anterior

oblique position and/or 30 ° in the right anterior oblique position if necessary) through the delivery sheath and pigtail catheter.

#### 8.8.7.2 LAA Assessment and Measurement

According to the angiographic results, the LAA morphology (cauliflower shape, cactus shape, chicken wing shape, windsock shape), the number and location of lobules, and the characteristics of comb muscles were evaluated; According to the preselected reference, measure the maximum diameter and effective working depth of the LAA ostium under different projection positions. Evaluate LAA and left upper pulmonary vein to determine whether there is pericardial effusion.

For centers that use TEE to guide LAAO surgery, LAA morphology, number of lobes, and characteristics of pectinate muscles can be evaluated before occlusion; Measure the maximum diameter and effective working depth of the LAA ostium; Confirm the position of the circumflex branch; Confirm that there is no thrombus or high-density echo in the left atrium and LAA.

#### 8.8.7.3 LAA occlusion

Select the appropriate Watchman occluder according to the LAA measurement size.

Under the protection and guidance of a pigtail catheter, deliver the delivery sheath of the occluder to LAA, and confirm the position of the sheath through angiography. Withdraw the pigtail catheter, send it into the pre-installed Watchman occluder, and lock the delivery sheath with the guide sheath. Under the monitoring of X-ray or TEE, the self-expanding occluder can be expanded by fixing the handle and removing the sheath. Confirm the position of the occluder and whether there is an obvious marginal shunt through angiography, and measure the compression ratio under the maximum lateral diameter of the occluder. The stability of the occluder was confirmed by the tug test. The presence of PDL and the maximum shunt size were evaluated by TEE multi-angle color Doppler blood flow.

When the occlusion position is not satisfactory, the release position of the occluder can be readjusted through recovery (full recovery/half recovery/micro recovery) and re-release operation under X-ray and/or TEE monitoring. If the adjustment is invalid, consider replacing the plug with a different size.

When the occlusion is satisfactory, release the device.

TEE assessed pericardial effusion.

#### 8.8.7.4 Definition of satisfactory occlusion

A satisfactory occlusion is defined as that LAAO meets the PASS criteria. The PASS criteria include: P (Position) position, the instrument is placed at the ostium of LAA or a slightly distant position; A (Anchor) anchoring, the fixed anchor has been embedded in the LAA wall, and confirms that the device is stable; S (Size) size, the device is compressed by 8%~20% relative to the original size; S (Seal) occlusion, the device occlusion is good, and the residual shunt is not more than 5mm.

#### 8.8.7.6 Intraoperative X-ray evaluation and data storage

During the LAAO operation, the X-ray images from LAA angiography (see 8.8.7.1 for details) to angiography evaluation before the release of the occluder (see 8.8.7.3 for details) are required to save the original files in DICOM format and submit the backup files to the central laboratory for quality control review.

#### 8.8.7.7 RFCA for AF after LAAO

After the completion of LAAO, the delivery sheath of the occluder was retained and sent to the left atrium through the multipole mapping catheter for three-dimensional reconstruction of the left atrium. After that, a cold saline catheter can be placed through this sheath or another sheath (the atrial septum needs to be punctured again or sent to the left atrium through the original puncture point) to perform RFCA for atrial fibrillation. See Section 8.8.6 for specific ablation scheme.

### 8.8.8 Postoperative precautions

#### 8.8.8.1 Resuscitation during the blanking period

If any symptomatic atrial arrhythmia occurs within the blanking period of 3 months after surgery, electrical cardioversion should be performed within 48 hours after the occurrence. If it exceeds 48 hours, drug cardioversion or electrical cardioversion is required after TEE excludes atrial/device-related thrombus.

#### 8.8.8.2 Postoperative anticoagulation regimen

If there is no contraindication of anticoagulation, anticoagulation treatment should be maintained within 3 months after operation. Those taking warfarin should maintain the target value of INR at 2-3, or take new oral anticoagulants. If no PDL  $\geq$  5mm is found in the TEE visit 45 days after the operation, the anticoagulant treatment can be stopped after the blank period, and the dual antiplatelet therapy (DAPT) can be used instead, that is, clopidogrel 75 mg od + aspirin 100 mg qn, with a course of 3 months. Six months after the operation, it can be changed to single antiplatelet therapy (SAPT), that is, clopidogrel 75 mg od or aspirin 100 mg qn for life.

If PDL  $\geq$  5mm or DRT is found during TEE follow-up after surgery, the duration of oral anticoagulation treatment should be extended regardless of whether the patient has thromboembolic events. It is recommended to recheck TEE after 2-3 months of treatment, and decide the next treatment strategy according to the results. At the same time, adverse events should be recorded (see 8.2 for details).

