8.9.3.7 TEE follow-up of occluder

- ✓ TEE follow-up evaluation of occluder, including occluder position, orientation, occluder marginal shunt (PDL), device related thrombus (DRT), incomplete endothelialization of occluder surface, delayed pericardial effusion, etc;
- ✓ If the results are unsatisfactory 45 days after the operation (i.e. PDL  $\geq$  5mm, and/or the surface of the occluder is not fully endothelialized), TEE can be re evaluated 3 months after the extended anticoagulation treatment or 6 months after the operation as appropriate;

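### The findings that permit stopping anticoagulation, call for extending it, and trigger a repeat TEE do not match between 8.8.8.2 and 8.9.3.7

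*Protocol*

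**What the plan says.** Protocol 8.8.8.2 keeps patients without contraindication on anticoagulation for 3 months after the procedure. If the 45-day TEE shows no PDL of 5 mm or more, "the anticoagulant treatment can be stopped after the blank period", with a change to antiplatelet treatment. No other finding enters that condition.

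The next paragraph of 8.8.8.2 sets the opposite course for a PDL at or above "5mm or DRT is found during TEE follow-up after surgery, the duration of oral anticoagulation treatment should be extended". On re-imaging it adds: "It is recommended to recheck TEE after 2-3 months of treatment".

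Protocol 8.9.3.7 lists what the follow-up TEE must assess, and DRT is on that list. It then defines an unsatisfactory 45-day result as a PDL of 5 mm or more "and/or the surface of the occluder is not fully endothelialized". DRT is not in the definition. For such a result TEE may be repeated "3 months after the extended anticoagulation treatment or 6 months after the operation as appropriate".

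The Table 1 note (#) gives the same repeat timing but does not define unsatisfactory. Section 5.2.5 gives 6 months after operation, or 3 months after the anticoagulation regimen is adjusted.

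**The concern.** The same TEE report can lead to different actions depending on which paragraph a site follows. Two findings are affected: DRT with a leak below 5 mm (or none), and incomplete endothelialisation without DRT or a large leak.

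The first stake is patient safety, since these rules decide who stays on anticoagulation with a thrombus on the device or an incompletely covered surface.

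The second is ascertainment. After day 45, TEE is done only if necessary (Table 1) or on demand (Appendix C). The list of triggering findings therefore largely decides who is imaged again and can have a DRT detected or followed. DRT, thromboembolic events and clinically relevant bleeding are all components of the primary endpoint in 3.1, and 14 centres will apply these rules.

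**Working it through.** No figure in the protocol depends on these rules, so the check is to list the possible day-45 findings and read each rule literally. A PDL below 5 mm includes no leak.

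| Day-45 finding | 8.8.8.2 stop condition met | 8.8.8.2 extend condition met | Unsatisfactory under 8.9.3.7 |
|---|---|---|---|
| PDL < 5 mm, no DRT, fully endothelialised | yes | no | no |
| PDL < 5 mm, DRT, fully endothelialised | yes | yes | no |
| PDL < 5 mm, no DRT, incompletely endothelialised | yes | no | yes |
| PDL < 5 mm, DRT, incompletely endothelialised | yes | yes | yes |
| PDL ≥ 5 mm, with or without the others | no | yes | yes |

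**DRT (rows 2 and 4).** Both conditions of 8.8.8.2 are met. In row 2, 8.9.3.7 does not class the result as unsatisfactory, so it does not settle the matter.

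**Endothelialisation (row 3).** Section 8.8.8.2 permits stopping and gives no ground to extend. Section 8.9.3.7 calls the result unsatisfactory and times one of its two repeat-TEE options from an extended anticoagulation that 8.8.8.2 does not provide for this finding.

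**Timing (side point).** Section 8.8.8.2 does not say when its 2-3 months begin. Taking 30-day months:
- counted from day 45: 45 + 60 = day 105 to 45 + 90 = day 135, against about day 180 for the 6-month option elsewhere;
- counted from the end of the 3-month blanking period: 3 + 2 = month 5 to 3 + 3 = month 6, which reaches the 6-month option.

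The 3-month recheck is common to all the sections.

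**Number affected.** The protocol gives no DRT rate. Assuming 2-5% of the 202 planned patients:
- 202 × 0.02 = 4.04, about 4;
- 202 × 0.05 = 10.1, about 10.

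This is an upper bound for the DRT overlap, because patients who have DRT together with a PDL of 5 mm or more (last row) are not in conflict. No range is offered for incomplete endothelialisation, as the protocol gives nothing to base one on.

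**The case against.** **DRT.** The stopping sentence is permissive. The paragraph after it is directive and specific: "the duration of oral anticoagulation treatment should be extended regardless of whether the patient has thromboembolic events". An attentive investigator would probably let the second qualify the first, and 8.8.8.2 itself recommends a TEE recheck after DRT, so DRT is not left without a re-imaging rule. This softens the conflict. It does not remove it, because the stop condition as written does not exclude DRT and 8.9.3.7 omits it from its definition.

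**Endothelialisation.** A reader might infer that such a patient is told both to stop and to extend. The text does not go that far. Section 8.9.3.7 belongs to the follow-up data list and governs repeat TEE; it orders no extension, and its 6-month option is compatible with stopping. What stands is a mismatch between the lists, plus a timing option that presupposes an extension not provided for.

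**Timing.** The wording is advisory throughout and the windows meet at 3 months. That stands, and timing is therefore only a side point.

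**A leak of exactly 5 mm.** A reader might infer a further contradiction, because 8.8.7.4 accepts an occlusion if "the residual shunt is not more than 5mm". The documents do not support it. That is a criterion for releasing the device at implantation. At follow-up, 8.8.8.2 and 8.9.3.7 both use 5 mm or more, so a 5 mm leak gets one consistent answer.

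**Primary endpoint.** A reader might infer that the rules distort the primary comparison. DRT is itself a component, and section 9 uses Kaplan-Meier analysis. If that means time to first event, a patient with DRT at day 45 has already had the event before the stop-or-extend decision, and later treatment cannot change that patient's primary result. The rules are also the same in both arms, and nothing in the protocol shows a bias between them.

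**Conclusion.** The inconsistency is real and limited. For DRT with a leak below 5 mm, the stop and extend conditions of 8.8.8.2 overlap, and 8.9.3.7 does not name DRT as a trigger. For incomplete endothelialisation alone, 8.9.3.7 recognises a finding that 8.8.8.2 does not. The difference in recheck timing is minor.

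The DRT overlap concerns at most about 4 to 10 of 202 patients, which rests wholly on the assumed 2-5% rate. The endothelialisation group is of unknown size. The weight of the point lies in patient safety and in consistent re-imaging between centres. Any effect on the primary endpoint would come through later detection of DRT and later events in patients without a day-45 DRT, and the protocol gives no means of sizing it. The point deserves correction but is not critical to the validity of the trial.

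**What to change.** The investigators should reconcile 8.8.8.2, 8.9.3.7, 5.2.5 and the Table 1 note (#), preferably in one decision table that each section refers to. It needs:
- one list of findings that bear on stopping, extending and repeating TEE, dealing explicitly with DRT and with incomplete endothelialisation;
- conditions worded so that no finding meets both the stop and the extend condition;
- one recheck time with a stated starting point;
- a definition of an unsatisfactory result that the Table 1 note can cite.

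Which findings belong on the list and which time applies are clinical decisions for the investigators. The cost is a protocol clarification and a site notice; sample size, endpoints and analysis are unchanged.

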#### 8.8.8.3 Anti-arrhythmic drugs

To avoid early recurrence, antiarrhythmic drugs should be taken within the blank period of 3 months after surgery. Amiodarone is recommended as the first choice for those without contraindications. For patients with contraindications of amiodarone, other Class III or Class Ic antiarrhythmic drugs may be considered. The specific medication scheme should be judged by the investigator. Antiarrhythmic drugs should be stopped at 3 months to evaluate clinical recurrence.

### 8.9 Postoperative follow-up

8.9.1 During the 1-year follow-up period after combined operation for atrial fibrillation, a total of 5 visits are required, which are from 12 hours after operation to before discharge, 45 days after operation, and 3, 6, and 12 months after operation. See Table 1 in Section 8.1 for the specific visit plan and time window. The first visit was conducted in the inpatient department, and the rest were conducted in the outpatient consulting room.

8.9.2 The contents of each follow-up visit shall be completed as required and recorded in the CRF form truthfully.

8.9.3 For each follow-up visit, the following data shall be collected from hospital records or communication with patients according to specific visit requirements (refer to Table 1 in Part 8.1 and Appendix C in Part 14 for data collection):

8.9.3.1 Medical examinations

- ✓ Collecting heart rate and blood pressure data.

8.9.3.2 Recurrence of atrial arrhythmia, the

- ✓ List records of patient-perceived episodes of atrial arrhythmia that have occurred since the last visit; the
- ✓ Provide the duration of the seizure.

8.9.3.3 The patient's current cardiac medications, the

- ✓ Record the cardiac drug treatment since the last visit, including antithrombotic drugs, AAD and other cardiac related drugs;

8.9.3.4 ECG information

- ✓ Provide ECG information of each visit, including heart rate, rhythm, QT interval and other results;

8.9.3.5 Ambulatory electrocardiogram

- ✓ List the episodes of atrial arrhythmia recorded on a 24-hour ambulatory electrocardiogram, providing the duration and frequency of the episodes.
- ✓ Preferably 7-day ambulatory electrocardiographic (ECG) monitoring, if available.

8.9.3.6 Evaluation of transthoracic echocardiography (TTE)

- ✓ It includes left atrial diameter (LA), left ventricular end diastolic diameter (LVEDd), left ventricular end systolic diameter (LVEDs), and left ventricular ejection fraction (LVEF);

8.9.3.7 TEE follow-up of occluder

- ✓ TEE follow-up evaluation of occluder, including occluder position, orientation, occluder marginal shunt (PDL), device related thrombus (DRT), incomplete endothelialization of occluder surface, delayed pericardial effusion, etc;
- ✓ If the results are unsatisfactory 45 days after the operation (i.e. PDL  $\geq$  5mm, and/or the surface of the occluder is not fully endothelialized), TEE can be re evaluated 3 months after the extended anticoagulation treatment or 6 months after the operation as appropriate;

#### 8.9.3.8 Thromboembolism event (TE)

- ✓ Symptomatic or non-symptomatic thromboembolic events, including ischemic stroke, transient ischemic attack, and systemic embolism, occurring since the last visit.

#### 8.9.3.9 Bleeding requiring intervention

- ✓ Bleeding events requiring intervention due to antithrombotic medication during the follow-up period, including bleeding from vital organ sites (e.g., cerebral hemorrhage, gastrointestinal hemorrhage, etc.) and hemorrhage.

### 8.10 Relapse and Reoperation

When all patients are followed up after the blank period, if symptomatic recurrence of atrial fibrillation is recorded, and AAD or synchronous DC cardioversion is invalid, radiofrequency ablation should be recommended again, and adverse events should be recorded.

8.10.1 The success rate of the re-ablation procedure will be analyzed separately from the success rate of the first procedure. The

8.10.2 All re ablation operations shall be recorded in the re operation part of CRF.

## 9. Statistical methods

The random grouping order and statistical analysis of this study were conducted using SPSS software (IBM, USA, version 26.0).

Continuous variables that conform to the normal distribution are expressed as mean  $\pm$  standard deviation, and those that do not conform to the normal distribution are expressed as median (interquartile range IQR). The comparison between groups is performed by t-test or analysis of variance; Classified variables are expressed in terms of rate or composition ratio, and compared between groups  $\chi^2$  Inspection; The results of all time event variables are represented by the median survival time; Kaplan Meier analysis was used to compare the survival rates of the primary endpoint events and the events without atrial fibrillation/ATA between the two groups. COX regression analysis was performed for subgroup analysis of primary endpoint events, and was represented by forest map.  $P < 0.05$  was statistically significant.

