Swaans and colleagues first published the single-center combined treatment experience of AF in the world In this study, 30 patients with AF with high risk of stroke or contraindication of anticoagulation were enrolled. They received the implantation of a Watchman occluder and RFCA in a single operation. After one year of follow-up, the maintenance rate of sinus rhythm without antiarrhythmic drugs (AAD) was 70%, and no thromboembolic event was found, which confirmed the feasibility and safety of the combined treatment of atrial fibrillation. Romanov et al. confirmed through a randomized controlled study that LAAO does not affect the success rate of RFCA for AF, thus providing further evidence-based medical evidence for the safety of combined treatment for AF Calvo et al. summarized the experience of combined treatment of AF with different types of left atrial appendage (LAA) occluders. The success rate of postoperative AF-free was 78%, and 97% of patients could safely stop anticoagulant drugs Phillips and colleagues first published the 5-year long-term follow-up results of combined treatment for AF, fully proving the long-term effectiveness and safety of this treatment. Our center was the first to publish a Chinese single-center study of combined treatment for non-valvular AF in China; then we published the first multicenter clinical study of combined treatment for AF in China, jointly with five centers within China. The results of these national and international studies have confirmed the effectiveness and safety of combined treatment for AF. These studies have confirmed the efficacy and safety of combined treatment for AF.

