## 3. Study endpoints

### 3.1 Primary endpoints

The primary endpoint was defined as the composite of thromboembolic events such as stroke/transient ischemic attack (TIA), device-related thrombosis (DRT), clinically relevant bleedings, and cardiovascular death or rehospitalization.

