### 5.2 Duration of the study

5.2.1 The duration of the study is 2 years, from 1 July 2020 to 30 June 2022.

5.2.2 Six months for ethical approval and coordination for all centers.

5.2.3 Patient enrollment at each center will last approximately 6 months, from July 1, 2020 to December 31, 2020.

5.2.4 Twelve months from enrolment to the last follow-up for all patients in the study; if necessary, the follow-up period should be extended to 2 years or more to assess the long-term outcomes.

5.2.5 Outpatient TEE or CTA reexamination on the 45th day after operation, and follow up at 6 months after operation or 3 months after adjusting anticoagulation regimen if necessary (see 8.9.3.7 for details);

5.2.6 The RFCA blanking period of AF is 3 months after operation. An outpatient follow-up visit at 3, 6, and 12 months postoperatively, and then every 6 months thereafter, for assessment of postoperative cardiac rhythms, medication records, echocardiographic evaluations, and records of adverse events (see section 8.1 for more details);

5.2.7 Patients may withdraw from the study at any time during the study for any reason. If a patient withdraws from the study, please refer to Section 8.4 Early Termination Procedures for Enrolled Patients for documentation.

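### Section 9 summarises every time-to-event result by a median survival time that is unlikely to be reached in 12 months, names only t-test or ANOVA for non-normal variables, and no section fixes the primary time point

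*Protocol*

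**What the plan says.** Protocol Section 9 fixes one summary for all time-to-event outcomes: "The results of all time event variables are represented by the median survival time". The next clause says "Kaplan Meier analysis was used to compare the survival rates of the primary endpoint events" and, likewise, freedom from AF/ATA. Cox regression is mentioned once: "COX regression analysis was performed for subgroup analysis of primary endpoint events".

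For continuous variables, Section 9 separates normal from non-normal when describing them; "those that do not conform to the normal distribution are expressed as median (interquartile range IQR"). It then gives a single rule for testing: "The comparison between groups is performed by t-test or analysis of variance". No rank-based test is named anywhere in the protocol.

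Section 3.1 defines the main outcome without a time point: "The primary endpoint was defined as the composite of thromboembolic events such as stroke/transient ischemic attack (TIA"), followed by device-related thrombosis, clinically relevant bleeding, and cardiovascular death or rehospitalization. Section 3.2.1, by contrast, ties the rhythm endpoint to one year and to long-term follow-up. Section 5.2.4 sets 12 months of follow-up for all patients and adds: "if necessary, the follow-up period should be extended to 2 years or more to assess the long-term outcomes".

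**The concern.** A Kaplan-Meier median can be read off only once the estimated curve has fallen to 50%. If most patients remain event-free at the end of follow-up, the prescribed summary is simply not reached, often in both arms, and it says nothing about how the arms differ. Because Section 9 applies the median to all time-to-event variables, this touches both the primary composite and AF/ATA freedom.

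The test for continuous variables does not follow the protocol's own distinction. A variable judged too skewed for a mean and standard deviation is still compared on its mean. The procedural endpoints in Sections 3.2.3 and 3.2.4 (occlusion time, fluoroscopy time, fluoroscopy dose) are plausibly of that kind.

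The time point is part of an endpoint's definition. Without one, and with an extension that has no stated criterion, the reader cannot tell which cut-off carries the primary result.

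**Working it through.** **Starting figures.** Section 9 contains no number to reproduce. The arm size comes from Section 7: 71 evaluable per group with 20% loss gives 71/(1 − 0.20) = 88.75, rounded up to 89, which agrees with the protocol. The planned number is 101 per arm.

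**1. Can the median be reached in 12 months?**

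Inputs from Section 1.2: 70% in sinus rhythm without antiarrhythmic drugs at one year, from a 30-patient study, so 30% with an event; and "The success rate of postoperative AF-free was 78"%, so 22% with an event. The 78% has no stated time point; taking it as about one year is an assumption. The composite event rate is not given, so a range is shown.

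With 12-month risk e and a constant hazard (assumption):
- median in months = 12 × ln 2 / (−ln(1 − e))
- cumulative risk at 24 months = 1 − (1 − e)²
- chance that at least 51 of 101 patients have an event by 12 months = upper binomial tail, with complete follow-up

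| 12-month risk | Median (months) | Risk by 24 months | P(at least 51 of 101 by 12 months) |
|---|---|---|---|
| 10% | 78.9 | 19% | 1 × 10⁻²⁴ |
| 20% | 37.3 | 36% | 8 × 10⁻¹² |
| 22% | 33.5 | 39% | 3 × 10⁻¹⁰ |
| 30% | 23.3 | 51% | 1.3 × 10⁻⁵ |
| 40% | 16.3 | 64% | 0.02 |
| 45% | 13.9 | 70% | 0.16 |
| 50% | 12.0 | 75% | 0.50 |

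For AF/ATA freedom (22–30%), the median lies far beyond 12 months. For the composite, it comes within reach only if the 12-month risk is close to 50%.

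**2. What does a t-test cost on skewed variables?**

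Assumptions, none of them from the documents: log-normal outcome, 101 per arm, one arm 25% longer, two-sided 5% level, log-SD s varied. Simulated power:

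| s | t-test | Rank test |
|---|---|---|
| 0.4 | 97% | 97% |
| 0.5 | 84% | 87% |
| 0.8 | 40% | 49% |
| 1.0 | 24% | 33% |

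Both tests kept a type I error near 5%. A hand check at s = 0.8:
- t-test: coefficient of variation √(e^0.64 − 1) = 0.947; standard error in units of the control mean 0.947 × √((1 + 1.25²)/101) = 0.151; 0.25/0.151 = 1.66; power about Φ(1.66 − 1.96) = 38%.
- Rank test: (ln 1.25/0.8) × √(101/2) × √(3/π) = 1.94; power about Φ(1.94 − 1.96) = 49%.

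Both agree with the simulation to within about two points.

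**3. Is a primary time point fixed?**

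Section 3.1 names none, and Section 9 names none. Section 5.2.4 gives 12 months but permits 2 years or more. The calendar does not settle it: enrolment from 1 July to 31 December 2020 and study end on 30 June 2022 (Sections 5.2.1 and 5.2.3) leave 18 to 24 months between enrolment and study end. By the first table, at a 30% one-year risk the cumulative risk is 30% at 12 months and 51% at 24 months, so even whether a median exists depends on the cut-off.

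**The case against.** **The median might be reached.** Only the 70% is tied to one year, and it comes from 30 patients. No composite rate is given, and the composite includes rehospitalization, which may be frequent. With censoring, a Kaplan-Meier curve can fall to 50% although fewer than half of the patients have an observed event, and an extension to two years could just bring a median into reach. This stands. A reader might infer that the median will certainly not be reached for any outcome; the documents support only very unlikely for AF/ATA freedom at 12 months, and leave the composite open.

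**The comparison is not lost.** A reader might infer that the trial would have no usable primary result. Section 9 already plans a Kaplan-Meier comparison of survival rates for both outcomes, so an unreached median would spoil the stated summary, not the comparison.

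**Effect measure and test.** A reader might also fault the absence of a hazard ratio or log-rank test. A statistical analysis plan that is not shown may supply these, and Section 9 assigns Cox regression to subgroups without saying it is used nowhere else. That is not part of this point.

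**The t-test is minor.** It affects secondary procedural endpoints, its type I error is sound, and at log-SD 0.4 to 0.5 the loss is 0 to 3 points. This stands as a limit on size. The mismatch between description and test remains.

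**The cut-off.** A reader might infer that the cut-off will be moved after the results are seen. Nothing links the extension to results: Section 5.2.4 ties it to long-term outcomes, the note to Section 8.2.4 treats the 12-month visit as the last, and Section 8.9.1 describes a one-year follow-up with five visits. These suggest 12 months is intended, but no passage says so for the primary composite.

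**Conclusion.** The point holds in a limited form and merits a wording correction.

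- **Median survival time.** It is a poor stated summary for 12 months of follow-up. For AF/ATA freedom at 22–30% risk, the chance that half of an arm has an event is about 10⁻⁵ or less. This rests on the Section 1.2 background rates applying here and on reading the 78% as roughly a one-year figure. For the composite, the conclusion depends on a rate that the protocol does not give; the threshold is about 50% at 12 months.
- **t-test or ANOVA for non-normal variables.** The cost is power, not validity: from nothing at log-SD 0.4 to about 9 points at 0.8 to 1.0, under an assumed log-normal shape and a 25% difference, on secondary endpoints only.
- **Time point.** The gap is in Section 3.1, and the open extension in Section 5.2.4 makes it matter.

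The first two items concern methods that Section 9 states, and the third concerns the endpoint definition itself. They should be corrected in the protocol; a later analysis plan that reported something other than the median would contradict Section 9 as it stands.

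**What to change.** - **Section 9, time-to-event results:** replace the median survival time with Kaplan-Meier event-free proportions at 12 months in each arm and their difference with a 95% confidence interval, for the primary composite and for AF/ATA freedom.
- **Section 9, continuous variables:** keep the t-test or ANOVA for variables treated as normal, and compare non-normal variables with the Wilcoxon rank-sum test.
- **Section 3.1:** state that the primary composite is assessed at 12 months.
- **Section 5.2.4:** state that the primary analysis is at 12 months and that any longer follow-up is secondary.

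The cost is wording in three sections. No extra visits, data or patients are needed.
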